5.4.6 Statistical analysis of secondary outcomes

The proportion of fallers versus non-fallers in each group will be compared by logistic regression adjusting for gender, age, centre and history of falling. Odds ratios and their associated 95% confidence intervals will be provided.

The proportion of multiple fallers versus single or non-fallers in each group will be compared over the 12 month trial period using logistic regression adjusting for gender, age, centre and history of falling.

The time to the first fall will be derived as the number of days from randomisation until the patient reports having a fall as detailed from the participant’s falls calendar, telephone notification form or self-reported questionnaire. Participants who have not had a fall will be treated as censored at their date of trial exit, or date of last available assessment or 365 days/trial cessation, as appropriate.

The proportion of patients yet to experience a fall between the two groups will be summarised by a Kaplan Meier survival curve. The risk of experiencing a fall between the two groups during follow up will be analysed by Cox Proportional Hazard regression adjusting for gender, age, centre and history of falling. Hazard ratios and their associated 95% confidence intervals will be provided. The proportional hazard assumption will be evaluated using Schoenfeld residuals. The median time to the first fall and its associated 95% confidence intervals will be estimated from this adjusted model.

The proportion of people with depression in each group will be compared over the 12 month trial period using logistic regression adjusting for gender, age, centre and history of falling.

The following secondary outcomes, Short Fall Efficacy Scale, Fear of falling and Activity of Daily living, Geriatric Depression Scale are continuous and will be measured at baseline, month 6 and month 12. Linear mixed models will be used to compare the two groups on these outcomes adjusting for gender, age and history of falling. Random intercepts for each patient will be included in the models. Model effects and their associated 95% confidence intervals will be provided.

The secondary outcome fracture (yes/no) will be measured at baseline, month 6 and month 12. The fracture rate between the two groups will be compared using correlated logistic regression estimated using Generalised Estimating Equations (GEE) with robust standard errors adjusting for gender, age and history of falling . Model effects and their associated 95% confidence intervals will be provided

Missing data and sensitivity analyses

Missing data will be assumed to be Missing At Random (MAR) in the aforementioned statistical methods. We will therefore investigate departures from this assumption in a sensitivity analysis using pattern mixture models and selection models.

Analysis of cohort group

Descriptive statistics will be presented for the cohort group.

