Patients wishing to take part in the REFORM study will be asked to return their completed consent form and screening questionnaire by post to the York Trials Unit. Researchers at the York Trials Unit will then assess the returned screening forms, for participant eligibility in the study. The participant will be asked to initial each of the statements on the consent form to indicate they agree with them. If however, a participant mistakenly places a tick or a cross in the boxes, these shall be taken as an indication of consent. Nevertheless, all due care will be taken to ensure that the participant initials the boxes as stated on the form.  Any patients who are under 65 years of age, reports having neuropathy, dementia or other neurological condition such as Parkinson’s disease, Alzheimer’s, multiple sclerosis, Lous Gehrig’s or Huntington’s disease, is unable to walk without the help of a walk aid such as a Zimmer frame or walker or person to assist, has had a lower limb amputation, or are unwilling to attend their podiatry clinic will be ineligible to take part in the REFORM study. All eligible, consenting participants will then be asked to complete a baseline questionnaire which may be completed on-line, if the participant prefers. All participants who return valid baseline data will be included in the REFORM cohort. Any participant reporting a score of 10 or more on the Geriatric Depression Scale [25] [26] ie more severe depression, will be referred to their General Practitioner.

Inclusion in the REFORM pilot study and REFORM trial is dependent on participants meeting the eligibility criteria as detailed in section 5.2.1; 5.3.2 and 5.3.3 respectively. Participants who are not eligible will be informed of this outcome and encouraged to complete follow-up questionnaires as part of the REFORM cohort. This cohort will be sent questionnaires at the same time points as participants in the REFORM trial ie monthly falls calendar; six monthly health related quality of life and cost questionnaire post assessment. The questionnaires will be the same as those used for the trial follow-up questionnaires. Participants in the REFORM cohort will be able to withdraw at any point during the study without having to state a reason. If, however the participant indicates the reason for withdrawal, this will be recorded. Data will be retained for all participants up to the date of withdrawal, unless they specifically request that their details are removed.

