5.3.3 Exclusion criteria

Participants will be excluded if they fulfil any of the following criteria:

1. The participant is known to have neuropathy.
2. The participant is known to have a neurodegenerative disorder.
3. The participant does not complete the baseline or run-in data collection instruments adequately ie fails to return baseline questionnaires.
4. Participant has had a lower limb amputation
5. The participant is unable to walk household distances (10 metres/32 feet) without the help of a walking aid such as a Zimmer frame or walker or person to assist. Patients who use a walking stick however, will be eligible for the study.
6. The participant is known to have dementia.
7. Participants are unable to read or speak English.

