Appendix 3: Data collection schedule

|  | Invitation | Baseline | 2/3 week follow-up | Monthly data collection | 1 & 3  months | 6 month follow-up | 12 month follow-up |
| --- | --- | --- | --- | --- | --- | --- | --- |
| Consent/Decline form | √ |  |  |  |  |  |  |
| Demographic questionnaire | √ | √ |  |  |  |  |  |
| Falls questions | √ | √ |  |  |  | √ | √ |
| Falls calendars |  |  |  | √ |  | √ | √ |
| Geriatric Depression score |  | √ |  |  |  | √ | √ |
| Resilience questions |  | √ |  |  |  | √ | √ |
| EQ-5D |  | √ |  |  |  | √ | √ |
| Short falls efficacy scale |  | √ |  |  |  | √ | √ |
| Fear of falling |  | √ |  |  |  | √ | √ |
| Activity of Daily Living |  | √ |  |  |  | √ | √ |
| Fracture data |  | √ |  |  |  | √ | √ |
| Economic evaluation |  | √ |  |  |  | √ | √ |
| Footwear assessment & advice* |  | √ | √ |  |  |  |  |
| Exercise demonstration and advice * |  | √ | √ |  |  |  |  |
| Foot posture index* |  | √ |  |  |  |  |  |
| Foot problems* |  | √ |  |  |  |  |  |
| Exercise footwear and orthotic compliance calendars* |  | √ |  | √ | √ | √ | √ |
| Orthotic prescription/review* |  | √ |  |  |  |  |  |
| Routine podiatry care (will continue outside of trial time as routine)* |  | √ | √ |  |  |  |  |

*Intervention group only

REFERENCES

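### The logistic regression for depression leaves out the baseline Geriatric Depression Scale score, which is already collected, and so gives up some power in that secondary comparison

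*Protocol*

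**What the plan says.** Section 5.4.6 of the protocol contains two analyses of depression.

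- **Binary.** "The proportion of people with depression in each group will be compared over the 12 month trial period using logistic regression adjusting for gender, age". The full list of adjustments is given by "using logistic regression adjusting for gender, age, centre and history of falling". No baseline depression term is named.
- **Continuous.** The scale is grouped with other scores: "Geriatric Depression Scale are continuous and will be measured at baseline, month 6 and month 12". For these, "Linear mixed models will be used to compare the two groups on these outcomes adjusting for gender, age and history of falling", with a random intercept for each patient.

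The baseline score is available. The Appendix 3 row "Geriatric Depression score" is ticked at baseline, 6 months and 12 months.

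People with high baseline scores can enter the trial. Section 5.1.5 provides that "Any participant reporting a score of 10 or more on the Geriatric Depression Scale" is referred to the GP, and in the same section "All participants who return valid baseline data will be included in the REFORM cohort". The seven items under "Participants will be excluded if they fulfil any of the following criteria" in section 5.3.3 do not mention depression. Section 5.4.4 analyses everyone as randomised.

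**The concern.** For an outcome that is a dichotomised depression score, the same person's score before randomisation would normally be expected to be one of the best predictors. The protocol applies this logic to falls: every falls model adjusts for falls history, the baseline counterpart of the outcome. The depression model uses the same list as the faller models, so it keeps falls history but omits depression's own baseline counterpart. Randomisation is stratified by centre only (section 5.3.8), so the design does not balance baseline depression either.

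Two things are at stake in this one secondary comparison: power that could be had at almost no cost, and adjustment for whatever chance difference in baseline depression arises between the arms. The protocol names the complete covariate list, and section 5.4.4 says the detailed analysis plan will be based on the protocol. A plan that follows the text would inherit the omission.

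**Working it through.** **The plan's own figures.** The protocol gives no figure for the depression comparison. Its only sample-size figure is 890 (445 per arm) for 50% versus 40% fallers. That figure reproduces: 388 per arm without continuity correction gives 388/0.9, or 432 per arm (864 in total); 408 with correction gives 454 (908 in total). With 10% loss, 445 per arm leaves 445 × 0.9 ≈ 400 analysed and gives 81.3% power. The 400 per arm is carried forward.

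**Assumptions (none given in the protocol).** Baseline and follow-up scores are standard normal with correlation rho. A participant is depressed at follow-up if the score exceeds the cut-off that yields the chosen prevalence in controls. Treatment shifts the follow-up score of every treated participant. The test is a two-sided 5% Wald test from logistic regression.

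**Check 1: 30% relative reduction, 400 per arm, 1,500 replicates.** Power with arm alone, then with arm plus baseline score:

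| Prevalence | rho 0.5 | rho 0.7 |
|---|---|---|
| 15% | 48% to 54% | 49% to 60% |
| 25% | 73% to 80% | 73% to 87% |
| 35% | 90% to 94% | 91% to 98% |

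The gains run from 94 − 90 = 4 points to 87 − 73 = 14 points. A repeat that took prevalence down to 10% gave about 3 to 15 points.

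**Check 2: a shift of 0.25 SD, 800 analysed, 600 replicates.**

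| Prevalence | rho 0.5 | rho 0.7 | rho 0.8 |
|---|---|---|---|
| 10% | 52% to 52% | 46% to 58% | 47% to 67% |
| 20% | 68% to 73% | 66% to 78% | 64% to 88% |
| 30% | 76% to 81% | 72% to 88% | 76% to 92% |

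At 10% prevalence and rho 0.5 there is no gain.

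**Where the gain comes from.** At 20% prevalence and rho 0.7 in check 2:

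- Without the baseline score: odds ratio 0.63, standard error of the log odds ratio 0.193. |ln 0.63|/0.193 = 0.462/0.193 = 2.39.
- With the baseline score: odds ratio 0.53, standard error 0.229. |ln 0.53|/0.229 = 0.635/0.229 = 2.77.

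The standard error rises by 0.229/0.193 − 1 = 19%, but the log odds ratio rises by 0.635/0.462 − 1 = 37%. The test statistic grows because the conditional odds ratio is further from 1. In the setting of check 1 the standard error also rises, from 0.176 to 0.212 at 25% prevalence and rho 0.7.

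**Unfavourable cases.** At 5% prevalence with a 30% reduction, power goes from 20% to 20% (rho 0.5) and from 18% to 22% (rho 0.7). With only a 10% reduction, gains are 0 to 8 points and power stays below 25% either way.

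**Validity.** With no true effect, 5% to 35% prevalence and rho 0.5 or 0.7, false-positive rates were 4.0% to 5.1% without the baseline score and 4.4% to 5.5% with it.

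**Chance imbalance.** At an assumed 25% baseline prevalence, the standard error of the between-arm difference is √(2 × 0.25 × 0.75/400) = 0.031. A gap of up to 1.96 × 3.1 ≈ 6 percentage points is ordinary chance.

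**The case against.** The strongest reply is that nothing here is invalid. Omitting a baseline covariate after randomisation leaves the error rate at its nominal level, as the check shows. Which prognostic covariates to use is an efficiency choice, and a detailed analysis plan was to follow. The listed secondary outcome is the scale itself, not the proportion depressed, and the linear mixed model of the continuous score may already use the baseline value as one of its repeated measurements. The size rests wholly on assumed inputs. The simulations also compare arm alone with arm plus baseline score, not with the protocol's four covariates, which may carry part of the same information.

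Most of this stands and limits the point. It does not remove it: the binary comparison will report its own result, its covariate list is spelled out in full rather than left open, and the mixed model does not bring baseline information into it.

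A reader might also infer three stronger things that the document does not support:

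- **That participants already depressed at entry dilute the comparison.** The outcome as written is the proportion with depression, not new cases, and people depressed at entry can improve. The simulations apply the treatment effect to them too, so they demonstrate no dilution.
- **That precision is lost.** On the reported log-odds scale the standard error is smaller without the baseline score. What is lost is power.
- **That a baseline imbalance would be mistaken for a treatment effect.** Chance imbalance is already covered by the 5% error rate. The planned model simply does not adjust for it.

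**Conclusion.** The point holds as a minor, inexpensive improvement to one secondary analysis. The depression logistic regression is valid on average but less powerful than it need be. The loss is about 3 to 15 points with 400 analysed per arm, 10% to 35% prevalence, correlation 0.5 to 0.7 and a 30% relative reduction. It could be larger at a correlation of 0.8 (16 to 24 points under a 0.25 SD shift), and is close to nil if depression is rare or the correlation is low. These are assumed inputs, and the protocol does not state what cut-off or time point will define depression in this model; the score of 10 in section 5.1.5 is a referral threshold. The primary outcome is not affected, and the mixed model of the continuous score softens the consequence for conclusions about depression as a whole.

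**What to change.** In section 5.4.6, add the baseline Geriatric Depression Scale score, as a continuous covariate, to the logistic regression for depression, alongside the four adjustments already listed. State that the resulting odds ratio is conditional on the baseline score.

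The cost is one extra term in one model. No new data are needed, and the covariate should be largely complete because section 5.3.3 excludes people who do not return the baseline questionnaire. The one real consequence is interpretive: the adjusted odds ratio is a different quantity from one that does not condition on baseline score, and will usually lie further from 1, so the two should not be compared as if they estimated the same thing.

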5.4.4 Statistical analysis

There will be one single analysis at the end of the trial. All analysis will be conducted using STATA, (StataCorp, version 10.1, 4905 Lakeway Drive, College Station, Texas 77845 USA) and SAS (SAS Proprietary Software version 9.2, SAS Institute Inc., Cary, NC, USA) All analyses will be conducted on an intention to treat basis, ie including all randomised patients in the groups to which they were assigned. If more than 890 participants are recruited and unequal allocation is utilised then analyses will be adjusted to take this into account. The trial statistician and health economist will write detailed analysis plans, based on the protocol after it has been approved.

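### The secondary repeated-measures models list baseline among the outcome times and omit the baseline value as a covariate, and the unweighted fracture GEE does not match the stated MAR assumption

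*Protocol*

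**What the plan says.** Section 5.4.6 of the protocol states that the Short Falls Efficacy Scale, fear of falling, activities of daily living and the Geriatric Depression Scale "are continuous and will be measured at baseline, month 6 and month 12". The model follows: "Linear mixed models will be used to compare the two groups on these outcomes adjusting for gender, age and history of falling". It adds: "Random intercepts for each patient will be included in the models". The section names no time term, no group-by-time term and no baseline score.

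For fracture: "The secondary outcome fracture (yes/no) will be measured at baseline, month 6 and month 12". The method is "correlated logistic regression estimated using Generalised Estimating Equations (GEE) with robust standard errors adjusting for gender, age and history of falling". No weighting or imputation is named.

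Under the missing-data heading in the same section: "Missing data will be assumed to be Missing At Random (MAR) in the aforementioned statistical methods". The GEE is one of those methods. Pattern mixture and selection models are planned as sensitivity analyses.

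Appendix 3 confirms that each of the four scales and the fracture data are collected at baseline, 6 and 12 months. Section 5.4.4 says: "The trial statistician and health economist will write detailed analysis plans, based on the protocol after it has been approved".

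**The concern.** The text lists baseline beside the two follow-up times as an occasion on which the outcome is measured, then compares the groups on that outcome with a covariate list that does not contain the baseline value. Two plain readings follow, and each has a cost.

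- **Baseline is one of the responses and a single group effect is fitted.** An occasion before randomisation, where the expected difference is zero, is averaged into the treatment effect. For fracture, events that treatment cannot have influenced are counted in the comparison.
- **Baseline is simply left out.** The estimate is unbiased, but a strong predictor that is already collected goes unused.

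Separately, the missing-data assumption is stated once for all methods. A likelihood-based mixed model fits that assumption. An unweighted GEE generally does not, because it needs data missing completely at random or missingness that depends only on the covariates. Robust standard errors do not change this.

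**Working it through.** **The plan's own figure.** The protocol gives no figure for these models, only the trial size (section 5.3.6: 50% versus 40%, 80% power, two-sided 5%, 10% loss). The two-proportion formula gives 388 per arm, or 408 with continuity correction. Dividing by 0.9 and rounding up gives 432 and 454 per arm, so 864 and 908 in total. The stated 890 lies between them and is reproduced within 3%. Analysed per arm: 445 × 0.9 = 400.5, taken as 400.

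**Assumed inputs (not in the protocol).** Unit variance, equal correlation ρ between any two occasions, the same true effect δ at 6 and 12 months, balanced data. For the worked case ρ = 0.6 and δ = 0.25 SD.

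**Continuous scales.** The variance of a difference between arms is 2V/400, with V per patient:

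- *Baseline as response, one group effect.* The random-intercept estimate is the difference in three-occasion means. Its expectation is (0 + δ + δ)/3 = 2δ/3 at any ρ, and V = (1 + 2ρ)/3. At ρ = 0.6: estimate 0.167, V = 0.733, SE = 0.061, z ≈ 2.75.
- *Baseline omitted.* Expectation δ, V = (1 + ρ)/2 = 0.80, SE = 0.063, z ≈ 3.95.
- *Baseline as covariate.* Expectation δ, V = (1 + ρ)/2 − ρ² = 0.44, SE = 0.047, z ≈ 5.3.
- *Baseline as response with an unconstrained group-by-time term, reporting change.* Expectation δ, V = 1.5(1 − ρ) = 0.60.
- *Baseline as response with arm means constrained equal at baseline.* No dilution. In a small simulation its mean and spread matched those of the covariate model.

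The cut in SE from adjusting, against omitting baseline, is 1 − √{[(1 + ρ)/2 − ρ²]/[(1 + ρ)/2]}. Power is Φ(z − 1.96), with δ chosen so that the covariate model has 80%:

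| ρ | Cut in SE | Power, one effect over three times | Power, baseline omitted | Power, change contrast |
|---|---|---|---|---|
| 0.5 | 1 − √(0.50/0.75) = 18% | 37% | 63% | 63% |
| 0.6 | 1 − √(0.44/0.80) = 26% | 30% | 55% | 67% |
| 0.7 | 1 − √(0.36/0.85) = 35% | 24% | 45% | 71% |

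**Fracture.** Assume 4% versus 3% per follow-up period and 4 to 8% in both arms at baseline.

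- Follow-up only: (0.03/0.97)/(0.04/0.96) = 0.74.
- Baseline 4% averaged in: intervention (4 + 3 + 3)/3 = 3.33%, control 4%; odds ratio (0.0333/0.9667)/(0.04/0.96) = 0.83.
- Baseline 8% averaged in: 4.67% versus (8 + 4 + 4)/3 = 5.33%; odds ratio (0.0467/0.9533)/(0.0533/0.9467) = 0.87.

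**GEE and missing data.** Assume true 12-month fracture of 5.88% (control) versus 4.72% (intervention), odds ratio 0.79. Let 12-month dropout depend on 6-month fracture, with 5% dropout among those without one. An unweighted GEE with independence working correlation then gives:

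- 40% dropout after fracture in both arms: 5.38% versus 4.35%, odds ratio 0.80.
- 40% in control, 10% in intervention: 5.38% versus 4.67%, odds ratio 0.86.

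**The case against.** The strongest reply is that the section states measurement times, not model terms. It nowhere says that the baseline value enters the outcome vector. No time term is named either, so the sentence is evidently not a full specification, and section 5.4.4 promises detailed analysis plans, which are not shown. Under two admissible readings, a group-by-time term or a baseline-constrained model, there is no dilution, and under the second no loss of precision either.

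Much of this stands. A reader might infer that the trial will report diluted effects. The documents do not support that, because shrinkage to two thirds needs both baseline as a response and a single group effect over all three times, and the text fixes neither. A reader might also infer that the protocol declares the GEE valid under MAR. It does not: it says missing data are assumed MAR and plans sensitivity analyses for departures.

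What remains is that the protocol does more than leave detail open. It names the occasions, the random effect and the covariates, and the baseline value is not among the covariates although it is collected. Later plans are to be based on the protocol, so one that followed this list would carry the omission forward. Nor does any stated weighting or imputation reconcile the GEE with the assumption made for it.

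**Conclusion.** The concern holds as a defect in the stated model wording. The baseline value is listed with the outcome times, is missing from the covariate list, and its role is not fixed. The consequence depends on the reading:

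- One group effect over three occasions gives two thirds of a constant true effect (at any correlation, in balanced data). On the assumed fracture rates it moves an odds ratio of 0.74 to between 0.83 and 0.87.
- Leaving baseline out causes no bias but forgoes a reduction of about 18 to 35% in SE for a correlation of 0.5 to 0.7.
- A baseline-constrained model suffers neither loss.

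The mismatch between the unweighted GEE and the MAR assumption is real. Its effect is probably small unless dropout after a fracture differs by arm: 0.79 became 0.80 with equal dropout and 0.86 with a 40% versus 10% split. The correlations, effect size, fracture rates and dropout rates are all assumptions. Only secondary outcomes are touched; the primary falls-rate analysis and the 890 are not affected.

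**What to change.** - **Continuous scales.** Take the 6- and 12-month scores as outcomes and the baseline score as a covariate alongside gender, age and history of falling, with time and group-by-time terms. Alternatively, keep baseline as a response with arm means constrained equal at that time. Say which.
- **Fracture.** Count only fractures after randomisation and use baseline fracture history as a covariate.
- **Missing fracture data.** Use a weighted or multiply imputed GEE, or state that the GEE assumes MCAR or covariate-dependent missingness. Collapsing to any fracture in 12 months with ordinary logistic regression would not settle this: a participant with no fracture at 6 months and no 12-month form has an undefined outcome, and a complete-case fit ignores the 6-month response. A random-intercept logistic model would change the odds ratio from marginal to patient-specific.

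The cost is wording in section 5.4.6 and the matching analysis plan, plus some programming if weighting or imputation is chosen. No new data are needed, since Appendix 3 already schedules every baseline variable.
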